#### **Treatment:**

Patients enrolled to the study will be administered NO-impregnated or non-NO-impregnated indwelling catheter for  $7-21 \pm 7$  days in addition to standard treatment given in the hospitals urology department and in the outpatient clinic.

**6.2 Study design and Scheduled Visits (Visit 1 – Visit 5)**

|                                                      | Screening and Enrollment (day 0) | Day of Operation and Catheterization (day 1) | Hospitalization (day 2 - discharge) | Catheter removal (day 7-21±7 days) | follow up Telephone call (day 21±3 days) | Follow up visit (day 30 –45) |
|------------------------------------------------------|----------------------------------|----------------------------------------------|-------------------------------------|------------------------------------|------------------------------------------|------------------------------|
| Visits                                               | Visit 1                          | Visit 2                                      |                                     | Visit 3                            | Visit 4                                  | Visit 5                      |
| Screening, signing informed consent and Enrollment   | +                                |                                              |                                     |                                    |                                          |                              |
| Physical exam                                        | +                                | +                                            | +                                   | +                                  |                                          | +                            |
| Catheter insertion                                   |                                  | +                                            |                                     |                                    |                                          |                              |
| Urine microbiological test (CFUs)                    | +                                | +                                            | +                                   | +                                  |                                          | +                            |
| Lab tests (CBC, biochemistry, bleeding)              | +                                | +                                            | +                                   | +                                  |                                          | +                            |
| Vital signs**                                        | +                                | +                                            | +                                   | +                                  |                                          | +                            |
| Catheter removal                                     |                                  |                                              |                                     | +                                  |                                          |                              |
| Post void residual urine volume                      |                                  |                                              |                                     | +                                  |                                          |                              |
| Questioner for demographics data and medical history | +                                |                                              |                                     |                                    |                                          |                              |
| Telephone call                                       |                                  |                                              |                                     |                                    | +                                        |                              |

\* Every day during hospitalization. At physical examination put emphasis on penis tissues such as the glans, shaft and prepuce.

\*\* Vital signs: heart rate, blood pressure, and temperature. During hospitalization, these will be done every 8 hours.

\*\*\* After catheter removal catheter specimens will be processed and evaluated for bacterial biofilm (see Appendix 1).

## **7. STUDY POPULATION**

### **7.1 Number of Patients**

A total of 12 patients, over the age of 18 undergoing radical prostatectomy will be enrolled.

The study is not expected to show statistical significance or statistical power, but to demonstrate a safety and tolerability profile.

6 patients will be catheterized with NO-impregnated Foley catheters followed by 6 patients catheterized with non-NO-impregnated Foley catheters.

### **7.2 Inclusion Criteria**

- Patients before radical prostatectomy at the urology department in Beilinson Medical Center, which will be catheterized for 7-21±7 days
- Age:  $\geq 18$  years
- Expected life expectancy of more than 12 months
- The investigator has completed a medical history and a physical examination to assure that the patient meets all study enrollment criteria
- The patient is willing and able to read, understand and sign the study informed consent form

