### 3. INTRODUCTION

#### 3.1 Background

According to recent publications by the World Health Organization (WHO) [1], hundreds of millions of patients are affected by health-care associated infections worldwide each year, resulting in prolonged hospital stays, long-term disabilities, deaths, and financial losses for health systems. The most common hospital-acquired infection is urinary tract infection (UTI), which accounts for almost 40% of all nosocomial infections [2]. According to the Center of Disease Control (CDC), most hospital-acquired UTIs are associated with catheterization [3]. In fact, urinary catheter-related bacteriuria is the most common health care associated infection worldwide [4]. Studies have showed that *Escherichia coli* is the most common bacterial pathogen responsible for catheter-associated UTIs (CAUTIs) [5, 6].

Planktonic bacteria can adhere to surfaces on catheters and colonize, creating a persistent environment called a biofilm [7, 8]. These colonies consist of bacteria that are highly differentiated and resistant to standard antibiotics [9], augmenting the potential of these pathogens to cause infections in patients with indwelling catheters.

In recent years, catheters coated with various antiseptic materials have been investigated for their ability to prevent biofilm formation and bacteriuria [10-13]. Several manufactures have marketed either antimicrobial-impregnated or silver-coated catheters as representing a technology to reduce CAUTI risk. More specifically, Nitric oxide (NO), an endogenously produced gas molecule, which plays an important role in host defense against various pathogens, has also been investigated for its potential to prevent biofilm formation [14, 15].

Using a novel approach, Regev-shoshani et al., generated antiseptic barrier on urinary catheters by impregnating them with NO [16]. Upon immersion in urine, these catheters demonstrated slow release of NO over a 14-day period and were able to prevent bacterial colonization and biofilm formation on their luminal and exterior surfaces [14]. In addition, they were also shown to inhibit the growth of *Escherichia coli* within the surrounding media and eradicated bacterial concentrations of up to  $10^4$  CFU/ml, suggesting the high potential of NO to prevent CAUTIs.

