### **NO-impregnated catheters Animal safety trials**

In February, 2014, ENOX conducted safety trials for the NO-impregnated catheters were in NZW rabbits. The experimental design included two equally-

sized groups (n=5, each group): one group was subjected to urethral catheterization with NO-impregnated indwelling urinary catheter, while the control group was subjected to urethral catheterization with non-impregnated indwelling urinary catheter. Safety-related parameters were evaluated following an exposure period of 7 successive days to the indwelling urinary catheter.

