## 6. STUDY DESIGN

### 6.1 Overview and Plan

This is a Prospective, Phase I, Open-label Case Series, Single-Center study.

A total of 12 patients, over the age of 18, undergoing radical prostatectomy will be enrolled. Screening data will be reviewed to determine patients' eligibility and informed consents will be obtained.

Patients who meet all inclusion criteria and none of the exclusion criteria will be enrolled.

6 patients will be allocated to receive NO-impregnated Foley catheters (treatment) followed by 6 patients allocated to receive non-NO-impregnated Foley catheters (control).

A patient will receive catheter up to  $21 \pm 7$  days of study treatment. A patient is considered as completed the study "per protocol", once study treatment was completed: 30-45 days after catheterization.

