### **8.3 Study Treatment**

#### **8.3.1 Operation and Catheterization – Visit 2 (day 1)**

- Perform a full physical examination
- Perform and record vital signs: temperature, blood pressure and heart rate
- Catheter insertion
- Perform urine test (microbiology and biochemistry), blood test for CBC, biochemistry, and coagulation: Prothrombin Time (PT), activated Partial Thromboplastin Time (aPTT), and International Normalized ratio (INR)

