#### **8.3.3 Catheter Removal – Visit 3 (day 7-21±7)**

- Remove Catheter\*\*
- Perform a full physical examination
- Perform and record vital signs: temperature, blood pressure and heart rate
- Perform urine test (microbiology and biochemistry) , blood test for CBC, biochemistry, and coagulation: Prothrombin Time (PT), activated Partial Thromboplastin Time (aPTT), and International Normalized ratio (INR)
- Measure post-void residual urine volume

\*\* After catheter removal catheter specimens will be processed according to protocol (see appendix 1).

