## 8.4 Follow-up Visits

### 8.4.1 Telephone call – Visit 4 (day 21±3)

- Perform a telephone call for follow-up and record any new medical conditions, AEs, or SAEs

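### The catheter duration of 7-21±7 days has no single lower limit, and its day-28 upper end does not fit the Visit 4 and Visit 5 windows, so observation after removal is short and uneven for late removals

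*Protocol*

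**What the plan says.** The duration in the inclusion criterion (Protocol 7.2, repeated in the Synopsis) is "which will be catheterized for 7-21±7 days". The same expression sets the objectives (4.1), the hypothesis (3.2), the treatment period (6.1, Treatment), the end-of-treatment assessment (7.4) and the removal visit, headed "Catheter Removal – Visit 3 (day 7-21±7"). None of these places says how to read a tolerance attached to a range. The overview in 6.1 words it differently: "A patient will receive catheter up to" 21±7 days, with no lower limit.

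The schedule around it is fixed in study days. Insertion is on day 1 ("Operation and Catheterization – Visit 2 (day 1")). The next numbered contact after removal is "Telephone call – Visit 4 (day 21±3"), whose task is: "Perform a telephone call for follow-up and record any new medical conditions, AEs, or SAEs". Visit 5 is on day 30-45 (8.4.2). The Synopsis counts it from surgery and 6.1 from catheterization; neither counts it from removal. Adverse events are followed until day 30-45 (11.2).

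The ITT cohort needs at least one day of catheter treatment. The Per-Protocol cohort needs completed treatment in compliance with the protocol and no major violation (13.3).

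**The concern.** The duration expression does three jobs. It decides who is eligible, it defines compliant exposure, and it states the range over which safety is to be claimed. An expression with no single lower limit cannot do these jobs consistently. There are six patients per group, so one patient classified differently is 1/6, about 17% of an arm.

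The upper end raises a separate problem. Adverse events, cultures and UTIs after removal are part of what this safety study observes, yet the follow-up contacts are tied to surgery and not to removal. Each later day of removal takes a day from the observation that follows it. The groups are enrolled one after the other without randomization, so nothing in the design balances dwell time or post-removal time between them. A safety conclusion for the whole stated range could then cover dwell times that no NO patient had, or had with only days of observation afterwards.

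**Working it through.** The protocol states no figure for post-removal observation, so there is nothing to reproduce. The check is interval arithmetic on the stated windows.

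**Inputs.** Duration 7-21±7 days (7.2, 8.3.3); ceiling of 21±7 days (6.1); insertion on day 1 (8.3.1); Visit 4 on day 21±3 (8.4.1); Visit 5 on day 30-45 (8.4.2); ITT minimum of one day (13.3).

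**Step 1: readings of the duration, each at its widest.**
- ±7 on both ends: 7-7 = 0 to 21+7 = 28. Zero days is not usable, because the ITT cohort needs at least one day of catheter treatment. In practice this is 1-28 days.
- ±7 on 21 only: 7 to 21+7 = 28 days.
- 6.1 taken alone: no lower limit, at most 21+7 = 28 days.

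The readings disagree only for dwell under 7 days. Such a dwell is allowed on the first and third readings and outside the range on the second. From 7 to 28 days all three agree.

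**Step 2: Visit 4 against removal.** The window is 21-3 = 18 to 21+3 = 24. A removal after day 24 must come after the call. A removal after day 18 can come after it.

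**Step 3: observation after removal.** Days from removal to Visit 5 run from 30 minus the removal day to 45 minus the removal day. Days from removal to Visit 4 run from 18 minus the removal day to 24 minus the removal day; a negative value means that the call comes first.

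| Removal day | Days to Visit 4 | Days to Visit 5 |
|---|---|---|
| 7 | 11 to 17 | 23 to 38 |
| 14 | 4 to 10 | 16 to 31 |
| 21 | -3 to 3 | 9 to 24 |
| 28 | -10 to -4 | 2 to 17 |

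**Step 4: sensitivity to the day count.** If 28 is a duration counted from insertion on day 1, removal falls on study day 29. The gap to a day-30 Visit 5 is then 1 day on the study-day scale. It stays at 2 days if Visit 5 is counted from catheterization.

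**Step 5: other passages at the short end.** Appendix 5 places the last blood pressure, coagulation and genital assessments 30 days after catheterization. Section 11.2 records concomitant medication only to day 30. On that timing a day-28 removal leaves 2 days and a day-21 removal leaves 9.

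**The case against.** The strongest reply is that this is a notation defect with little practical effect.

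- **Lower limit.** Section 6.1 attaches the ±7 to 21, which favours 7-28 days, and a ceiling there does not contradict a floor stated elsewhere. The criterion is prospective, and no passage describes a planned dwell under 7 days. Unplanned early removal is handled: assessments continue (7.5.1, 8.6) and the patient stays in the ITT cohort after one day. This stands as a limit on the size of the problem. It does not settle the reading, because the protocol never states one and Per-Protocol membership depends on it.
- **Visit 4.** The call only records new conditions and adverse events, which works with the catheter in place. That is right: no data are lost. What is lost for late removals is a contact after removal.
- **Visit 5.** Two days needs both windows at their extremes. Total observation is 30-45 days for every completer, unscheduled visits are allowed (8.5), and related SAEs stay reportable for up to 30 days after the last visit (Section 12). This stands, but the SAE rule does not cover non-serious events, cultures or most UTIs.
- **Listings.** Section 13 already lists all measured and derived variables individually. That makes the fix cheap; it does not reconcile the windows.

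Some stronger inferences are tempting and fail. A reader might take zero days as an allowed dwell; the ITT definition and insertion on day 1 rule that out in practice. A reader might divide 38 by 2 and report a 19-fold difference in follow-up, but that sets opposite corners of two windows against each other. A reader might say that 28 days contradicts the cited "slow release of NO over a 14-day period" or the rabbit study, assessed "following an exposure period of 7 successive days to the indwelling urinary catheter". Those passages report an in-vitro finding and an animal exposure. Neither claims to cover 28 days, and Appendix 5 says openly that this is first human use. Nor does Visit 3 conflict with the inclusion criterion, since it repeats the same expression.

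**Conclusion.** The concern holds in a limited form. The lower limit is undefined, which matters only for dwell under 7 days, planned or actual, and then decides compliance and Per-Protocol membership. The upper end of day 28 does not fit the follow-up schedule. The Visit 4 call comes before any removal after day 24, and observation from removal to Visit 5 falls from 23-38 days for a day-7 removal to 2-17 days for a day-28 removal.

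The two-day figure is an extreme, not an expected value. The protocol gives no distribution of dwell times, so how many patients would be affected cannot be estimated. The result assumes the ±7 is read at its widest and removal is counted in study days; counting 28 as a duration moves the minimum by at most one day. Nothing here shows that the primary safety listing would be wrong. The point is that the plan, followed as written, lets a late-removed patient finish with only days of post-removal observation and lets the conclusion extend to dwell times that nobody had. This should be corrected, because doing so costs little.

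**What to change.** The passages on duration and visit timing must be reconciled. The sponsor and investigators should:

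1. State one minimum and one maximum catheter duration and use them identically in the inclusion criterion, objectives, hypothesis, 6.1 and the Visit 3 heading, so that Per-Protocol compliance refers to the same limits. Which values are right is for them to decide.
2. Reconcile the Visit 4 and Visit 5 windows with that maximum, and Appendix 5 and the concomitant-medication cut-off with the result.
3. List actual dwell and days observed after removal for each patient. Placement and removal dates are already source data (18.2).
4. Limit the safety conclusion to the dwell times observed in the NO arm.

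The cost is protocol wording and one listing for 12 patients. The downside is a somewhat narrower safety claim.

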### 7.3 Exclusion Criteria:

- A urinary culture demonstrating UTI before surgery
- A patient with an indwelling urinary catheter prior to surgery
- Life expectancy of less than 12 months
- Concurrent illness, disability or geographical residence that would hamper study participation
- Patients with underlying diseases such as heart disease, lung disease, skin disease or infection involving the penis, scrotum and groin, immunocompromised patients (transplant recipients, HIV carriers)
- Patients with known ureteral stricture
- Patients with recurrent UTIs
- Current participation in another clinical investigation of a medical device or a drug or has participated in such a study within 30 days prior to study enrollment

### 7.4 End of Treatment Assessments (after completing 7-21±7 days of study catheterization)

End of study assessment include:

- AEs and SAEs
- Bacterial detection on catheters and culture from catheters and urine
- Vital signs measurements

### 7.5 Early Treatment Discontinuation

End of treatment assessments should be completed for all patients who prematurely discontinue from the study. This includes patients who were screened even though they were not exposed to the NO-impregnated catheter.

Every attempt should be made to follow the early discontinued patients according to the regular scheduled visits as per protocol. The patients who prematurely discontinue the study should be followed and treated by the investigator in a customary manner. Patients who decide not to continue with any further visits should complete the end of treatment assessment discontinuation.

#### 7.5.1 Criteria for Treatment Discontinuation

- AEs that are suspected to be related to NO-impregnated catheters, according to physician discretion

- Blood pressure and heart rate above or below the 20% of the normal ranges for the patient baseline

A patient whose treatment was discontinued for any reason should complete all study assessment including the follow up visits.

Concomitant medication (i.e. antibiotics) given during the study will not be a reason for treatment early discontinuation.

### **7.5.2 Criteria for Early Study Withdrawal**

A patient may withdraw or be withdrawn from the study for the following reasons:

- 1) Patient withdrew consent.
- 2) Protocol violation/ non-compliance.
- 3) Loss to follow-up/failure to return.
- 4) Patient with difficulty in insertion of catheter during surgery.
- 5) In cases which require catheter replacement.
- 6) Serious adverse event

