## 5. STUDY END POINTS

### 5.1 Primary End Point(s)

#### **Safety:**

- Determine AEs and SAEs associated with NO-impregnated catheters
- Proportion of patients (%) who prematurely discontinued the study due to AEs or SAEs

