**The following information should be provided to accurately and completely record the event:**

- 1) Investigator name
- 2) Patient number
- 3) Patient initials
- 4) Patient demographics
- 5) Clinical event
  - Description of the event
  - Date of onset
  - Severity of the event
  - Treatment
  - Relationship to study catheter (causality)
  - Actions taken regarding study catheter
- 6) If the AE results in Death
  - Cause of death (whether or not the death is related to study catheter)
  - Autopsy findings (if available)
- 7) Medical history CRF (copy)
- 8) Concomitant medication case report (copy of relevant CRF page )
- 9) Any relevant reports (laboratory, discharge, x-Ray, etc.)

This information should be sent to the sponsor.

The procedures for notification of suspected serious unexpected adverse reactions (SUSARs) shall be carried out in accordance with the Israeli MOH. SAEs should be reported by the ENOX BIOPHARMA to EC/IRB according to local requirements.

Patients who have had an SAE during the treatment period must be followed clinically until all parameters (including laboratory) have either returned to normal or have stabilized or are otherwise explained.

Any newly emergent SAEs, after treatment is discontinued or the patient has completed the study and is considered to be related to the investigational medicinal product (IMP) or study participation, should be recorded and reported immediately. The post-study period for the purpose of SAE reporting is routinely up to 30 days following last study visit or until SAE is resolved or stabilized.

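### An SAE can be handled either as stopping the catheter or as leaving the study, and the discontinuation endpoints count only leaving the study, so the same event can score 0 or 1

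*Protocol*

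**What the plan says.** Section 7.5.2 (Criteria for Early Study Withdrawal) begins "A patient may withdraw or be withdrawn from the study for the following reasons" and ends its list with "6) Serious adverse event". The item is not limited by relatedness to the catheter, by timing or by outcome.

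Section 7.5.1 (Criteria for Treatment Discontinuation) is about the catheter. Its first criterion is "AEs that are suspected to be related to NO-impregnated catheters, according to physician discretion", and it then says "A patient whose treatment was discontinued for any reason should complete all study assessment including the follow up visits".

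Three other places ask for continued follow-up:
- Section 7.5: "Every attempt should be made to follow the early discontinued patients according to the regular scheduled visits as per protocol". It also asks for end-of-treatment assessments in everyone who leaves early.
- Section 8.6: documented attempts to follow patients who discontinue. The section treats treatment and study discontinuation together and refers back to 7.5 for the criteria.
- Section 12: "Patients who have had an SAE during the treatment period must be followed clinically until all parameters" have normalised, stabilised or been explained.

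The second primary safety endpoint in 5.1 is "Proportion of patients (%) who prematurely discontinued the study due to AEs or SAEs". The tolerability endpoint is the same proportion restricted to events associated with the NO-impregnated catheter. Section 13 plans 95% confidence intervals for discontinuation. Section 13.4 adds the number failing to complete the study and a time-to-withdrawal analysis.

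**The concern.** The protocol has two routes after a serious event: stop the catheter and stay in the study (7.5.1), or leave the study (7.5.2). A serious event suspected to be caused by the catheter while it is in place qualifies for both, and nothing gives one route precedence.

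This would be only a drafting matter if the endpoints did not depend on the route. They do. Both discontinuation endpoints count patients who left the study, so the result follows the route chosen and not the clinical event. The study is open label, with 6 treated patients followed by 6 controls, so whoever chooses knows which catheter the patient has.

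The gap also runs the other way. A catheter taken out early because the patient could not tolerate it is what a tolerability endpoint should detect. If 7.5.1 is followed and the patient completes Visit 5, he has not discontinued the study and is not counted.

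**Working it through.** The protocol gives no figure to reproduce here: the 12 patients were chosen by judgement and no SAE rate is stated. The check is a comparison of passages, followed by the size of the consequence.

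**Step 1. One event, two routes.** Take one patient in the NO arm with a serious event during catheterization that is suspected to be catheter-related.

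| | Handled under 7.5.1 | Handled under 7.5.2, item 6 |
|---|---|---|
| Catheter | stopped | stopped |
| Study status | stays in, all visits | withdrawn |
| Safety discontinuation endpoint (5.1) | 0 | 1 |
| Tolerability endpoint (5.1) | 0 | 1 |
| Completer cohort (13.3) | in | out |
| Time to withdrawal (13.4) | no event | event |

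**Step 2. Reach beyond the double-covered case.** Item 6 does not require relatedness, and Section 12 counts prolonged or repeated hospitalization as serious. An unrelated surgical complication can therefore also lead to withdrawal at discretion and count in the safety endpoint. It would not count in the tolerability endpoint, which is limited to catheter-associated events.

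**Step 3. Size.** Inputs: n = 6 per arm (6.1 and 7.1), one SAE in the arm, no other AE-related discontinuation. Exact (Clopper-Pearson) 95% limits:
- 0/6 = 0%. Upper limit 1 − 0.025^(1/6) = 45.9%, so the interval is 0 to 45.9%.
- 1/6 = 16.7%. Lower limit 1 − 0.975^(1/6) = 0.4%. The upper limit solves (1−p)^6 + 6p(1−p)^5 = 0.025, giving p = 64.1%. The interval is 0.4 to 64.1%.

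Each such decision moves an arm's proportion by 1/6 = 16.7 percentage points.

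**Step 4. How likely the choice is to arise.** This needs an assumed per-patient SAE probability p. The chance of at least one SAE is 1 − (1−p)^n:

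| Assumed p | Arm of 6 | All 12 |
|---|---|---|
| 5% | 26% | 46% |
| 10% | 47% | 72% |
| 20% | 74% | 93% |
| 30% | 88% | 99% |

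These figures cover any SAE. The narrower case in Step 1 (during catheterization and suspected related) is less frequent, and the protocol gives no basis for its rate.

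**Step 5. Effect on the test.** Fisher's exact two-sided p for 1/6 against 0/6 is 1.00, so the choice changes the descriptive estimate and not a test result.

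**The case against.** The strongest reply is that the protocol already protects the data. Section 7.5 asks for the scheduled visits to be attempted in patients who discontinue, 8.6 repeats the request, and Section 12 makes clinical follow-up of SAEs mandatory. The other primary safety endpoint records catheter-associated AEs and SAEs whether or not the patient leaves, and 13.4 discusses SAEs case by case. This stands. A reader might infer from 7.5.2 that data collection ends at an SAE; the documents do not support that. Loss of Visit 5 is possible, because 7.5 lets patients decline further visits and Section 12 names no protocol visits, but it is not prescribed.

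A reader might also infer that every SAE produces an endpoint event. It does not: 7.5.2 is permissive. The permissive wording does not cure the problem, however, because it is what leaves the score to discretion.

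The contradiction has limits too. Section 7.5.1 covers only patients whose catheter treatment was discontinued, so an SAE after routine removal at Visit 3 lies outside it.

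Section 6.1 links completing the study to completing study treatment, so early catheter removal might be read as not completing. That would score 1 on either route, but the endpoint names the study and 7.5.1 keeps such a patient in it. The text does not settle the matter.

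Finally, one SAE withdrawal would leave fewer than 6 completers in an arm, since 7.5.4 recruits only up to 12. Any dropout does that, so it is a separate matter and carries no weight here.

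**Conclusion.** The point holds as an endpoint-definition defect caused by two overlapping discontinuation rules. Followed as written, the same serious event can give 0/6 or 1/6 on the safety discontinuation endpoint and, if catheter-associated, on the tolerability endpoint, according to an unblinded choice. A catheter stopped for intolerance in a patient who completes follow-up is missed by the tolerability endpoint.

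The shift is 16.7 percentage points per patient in an arm of 6, assuming a full arm and no other AE-related discontinuation. The two exact intervals overlap widely and no significance result changes. The protocol disclaims power, though, and offers the descriptive safety profile as its main output, so an ambiguous primary proportion matters. The documents do not support a claim that SAE outcomes are necessarily lost. The change should be made before enrolment, but it does not call the whole design into question.

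**What to change.** 1. Reconcile 7.5, 7.5.1, 7.5.2, 8.6 and Section 12 so that stopping the catheter and leaving the study are two separately recorded events, and state how an event that meets both lists is classified.
2. State that patients with an SAE remain in the scheduled data collection to Visit 5 unless consent is withdrawn. This concerns data collection only. Clinical decisions, including those about the catheter, remain with the investigator, and no clinical rule is proposed here.
3. In 5.1 and the matching synopsis text, define the discontinuation endpoints as premature catheter removal due to an AE or SAE (catheter-associated for tolerability). The word premature is needed because every catheter is eventually removed. Report study withdrawal, with reasons, separately.
4. Carry the same definition into the discontinuation proportions in Section 13 and the completion and time-to-withdrawal analyses in 13.4.

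The cost is a small text edit to the endpoint, discontinuation and analysis sections. It is more than deleting one list item, but it adds no visits, procedures or patients.
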